## **1. BACKGROUND/RATIONALE/PRESENT STATE OF KNOWLEDGE**

### **1.1. Overall Aim:**

About one to three percent of adults in Canada have an intellectual and developmental disability (IDD), and 20-40% of them have severe behavioural problems (SBP), including self-injurious behaviour, disruptive behaviour, or aggression. SBP are common contributors to morbidity and reduced quality of life for adults with IDD and their families. Current medications for SBP show equivocal effectiveness and are associated with a high risk of side effects. Innovative and safe treatments are urgently needed to increase quality of life and reduce morbidity, caregiver burden, and health care costs. While preclinical studies, anecdotal reports, and uncontrolled studies link SBP with an endocannabinoid mechanism and suggest that medical cannabinoids may be an efficacious and safe alternative to current medications for SBP in adults with IDD, rigorous evidence is still in the very early stages. Unlike cannabidiol (CBD), a cannabinoid with elusive mechanisms and dose ranges, nabilone, a marketed synthetic cannabinoid, has a clearer mechanism, favourable safety profile, and more predictable dosing. Data of safety and efficacy regarding nabilone in this population has never been published. Parallely, evaluating the effects of nabilone using MRI (especially fMRI and H MRS, which measure brain function and metabolism, respectively) optionally in some participants has the potential to reveal mechanisms underpinning behavioural changes post-treatment, thereby facilitating the development of better designs in using cannabinoid for SBP in IDD. Thus, we propose to conduct this investigator-initiated Phase I pre-pilot open-label clinical trial.

**Primary Aim 1:** To collect preliminary data on the tolerability and safety profile of nabilone in adults with IDD.

**Hypothesis 1:** To evaluate tolerability, we hypothesize that 80% of participants will complete the study protocol.

**Hypothesis 2:** To evaluate safety, we hypothesize that nabilone will be satisfactorily tolerated and have a favourable safety profile in adults with IDD, as quantified by lower rates of adverse events (AEs) and serious adverse events (SAEs) than those reported in the literature of antipsychotics in IDD.

**Exploratory Aim 2:** We will explore changes in SBP, as well as brain changes on MRI, which is optional, in participants pre-and post-treatment.

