### **1.2. The Need for More Research to Develop Innovative Treatment for SBP in Adults with IDD:**

About 1-3% of adults in Canada have an intellectual and developmental disability (IDD) (1), and 20-40% of them have severe behavioural problems (SBP), including self-injurious behaviour, disruptive behaviour, or aggression (2), in the absence of a confirmed psychiatric diagnosis. These SBP are associated with emotion dysregulation, pain, and sleep problems (3). SBP are major contributors to morbidity, functional impairments, missed opportunities for learning, reduced quality of life, and burden on families, health, education and disability sectors (4).

SBP in adults with IDD are extremely difficult to treat. Although psychosocial interventions are generally considered first-line treatments per national and international guidance (5, 6), for a subgroup of people with IDD and SBP, these options are not effective. Antipsychotics and other psychotropic medications are thus prescribed for up to 70% of adults with IDD (7, 8), off-label, and with equivocal efficacy (9). Further, people with IDD, relative to those without IDD, are at a higher risk of side effects of psychotropic agents and less able to report side effects (10, 11). These side effects include weight gain, metabolic disturbances, neurological symptoms, and avoidable death (12). Finally, because of suboptimal responses to currently available medications, polypharmacy is commonly used to treat SBP in adults with IDD (8), potentially leading to more adverse events (9). Thus, innovative and safer interventions are pressingly needed for this population.

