## **2. STUDY OBJECTIVES**

To address the current state of evidence for nabilone use to treat SBP in adults with IDD, we propose to conduct the first Phase I pre-pilot open-label clinical trial with the following aims and hypotheses:

**Primary Objective:** To collect preliminary data on the tolerability and safety profile of nabilone in adults with IDD.

Hypothesis 1: To evaluate tolerability, we hypothesize that 80% of participants will complete the study protocol.

Hypothesis 2: To evaluate safety, we hypothesize that nabilone will be satisfactorily tolerated and have a favourable safety profile in adults with IDD, as quantified by lower rates of AEs than those reported in the literature of antipsychotics in IDD.

**Exploratory Objective:** We will explore changes in SBP, as well as brain changes on MRI, which is optional, in participants pre- and post-treatment.

Significance/Innovation:

This is the first study to investigate nabilone for SBP in people with IDD. We will conduct a Phase I open-label trial to assess nabilone safety in this population, but with a fixed dosage range since it is an already marketed product (40). Findings from this project will inform the design of a series of clinical trials led by the PI in the future, i.e., a next-stage Phase I/II pilot placebo-controlled RCT to test the feasibility of a large-scale RCT, followed by a Phase II/III multicentre RCT to test available options for this difficult-to-treat clinical problem (Fig. 1). The planned trial will address an evidence-practice gap in the use of cannabinoid to meet a pressing need for services, the community and families, which has been identified as a priority research area by adults with neurodevelopmental disabilities, family members and clinicians in an Ontario-wide priority setting exercise (rb.gy/thr2od).

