#### Exclusion Criteria

- 1) History of hypersensitivity to any cannabinoid.
- 2) The presence of an unstable seizure disorder as defined by having not been seizure-free for at least 6 months or anticonvulsant treatment has not been stable for at least 4 weeks.

- 3) The presence of any clinically significant or unstable medical conditions, including cardiovascular, liver, kidney, pulmonary disease, presence of known congenital brain malformation, as per investigator assessment based on medical history and chart review.
- 4) The presence of a lifetime diagnosis of psychotic disorders, bipolar disorder, or substance use disorder, or current diagnosis of major depressive disorder or dementia, based on past psychiatric history noted in the medical chart, as well as Moss-PAS (ID) at S-V.
- 5) Family history of psychotic disorders.
- 6) Change in psychotropic medications less than 4 weeks prior to study drug use.
- 7) At the time of screening, each adult's medication list will be checked for drugs that are known to cause interactions with nabilone. When a given adult is taking any drugs or is taking a given medication exceeding a given dose) in the following list, he/she/they will be excluded.
  - a. Currently on benzodiazepines at the dose more than the benzodiazepine equivalent to lorazepam 2 mg daily.
  - b. Currently on medical psychostimulant, including methylphenidate (100 mg daily), lisdexamfetamine (70 mg daily), amphetamine/dextroamphetamine (Adderall XR®, 50 mg daily), dextroamphetamine (Dexedrine®, 50 mg daily) at the dose exceeding their respective maximum doses (as shown in the bracket after each agent) to treat ADHD in adults, based on the CADDRA guideline, [www.caddra.ca](http://www.caddra.ca).
  - c. Currently on nonbenzodiazepine hypnotics, including zaleplon (10 mg daily), zolpidem (10 mg daily), and zopiclone (7.5 mg daily), at the dose exceeding their respective suggested safety doses (as shown in the bracket after each agent), based on Canadian Recalls and Safety Alerts (<https://healthycanadians.gc.ca/recall-alert-rappel-avis/>).
  - d. Currently on any opioids.
  - e. Currently on barbiturates.
  - f. Drinking any alcohol one week before the screening visit.
  - g. Recreational use of any psychomimetic drugs, including Ketamine, LSD, MDMA, Magic mushrooms, PCP, Salvia, GHB, Bath salts, Methamphetamine; the last use happens within one week before the screening visit.

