#### Other measures

1. Demographic questionnaire
2. Current and Concomitant medications (including type, dose, and duration of treatment)\*
3. Height
4. Weight
5. Vital signs (blood pressure, heart rate, and temperature)
6. Drug diary to evaluate compliance

---

\*The high dose of benzodiazepine (more than the benzodiazepine equivalent to lorazepam 2 mg daily) and other cannabinoids, which are still used 4 weeks before the start of the use of the study drug (titration phase), are not permitted. Other concurrent medications and non-medication treatments (including behavioural therapy, psychological therapy, occupational therapy, support group etc.) are permitted before and during the trial.

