## **8. SAMPLE SIZE AND DATA ANALYSIS**

To test the Hypotheses 1 and 2, we aim to enroll 40 patients to enter the dose titration phase, consistent with common sample sizes for Phase I trials (63).

We assume the attrition rate of 25% from the dose titration phase to entering the open-label phase. To test behavioural changes at the group level (Exploratory Objective), the sample size of the remaining participants (N=30) could be sufficient to detect differences with effect size Cohen's d as low as of 0.53, and at power = 0.8 and two-sided  $\alpha$ -level = 0.05 (G\*Power 3.1), which is similar to that detected in the study investigating the effects of nabilone on agitation associated with dementia (27).

Paired-t test will be used to investigate the pre- vs. post-treatment behavioural and brain changes. Exploratory analyses will be performed to determine predictors of response including baseline individual features, using logistic regression. Safety profiles will be described in the percentage of each adverse effects. For MRI measures, non-parametric tests will be used to explore the brain changes with nabilone treatment, assuming that only few participants can finish MRI scans eventually.

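### Hypothesis 2 judges nabilone against antipsychotic adverse-event rates, but participants may stay on an antipsychotic, so the measured rate mixes nabilone alone with nabilone added to the comparator

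*Protocol*

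**What the plan says.** Section 2 of the protocol measures favourable safety "as quantified by lower rates of AEs than those reported in the literature of antipsychotics in IDD". Section 1.1 states the same criterion and adds serious events: "as quantified by lower rates of adverse events (AEs) and serious adverse events (SAEs) than those reported in the literature of antipsychotics in IDD". Neither section gives a numerical rate for the comparator.

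The eligibility and medication rules let antipsychotic users in and let them continue:

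- Exclusion 6 in Section 3.3 bars only a recent alteration: "Change in psychotropic medications less than 4 weeks prior to study drug use". A stable antipsychotic passes.
- Exclusion 7 says that "each adult's medication list will be checked for drugs that are known to cause interactions with nabilone", then lists benzodiazepines, psychostimulants and hypnotics above a dose limit, opioids, barbiturates, alcohol and recreational drugs. Antipsychotics are not on the list. Section 7.2 does not name them among the drugs to be discontinued either.
- The footnote to Other measures in Section 3.4 restricts high-dose benzodiazepines and other cannabinoids, then says: "Other concurrent medications and non-medication treatments (including behavioural therapy, psychological therapy, occupational therapy, support group etc.) are permitted before and during the trial".

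Section 1.2 indicates that background use is likely to be common: "Antipsychotics and other psychotropic medications are thus prescribed for up to 70% of adults with IDD". It adds that polypharmacy is usual in this population.

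On analysis, Section 8 says: "Safety profiles will be described in the percentage of each adverse effects". Table 1 marks the UKU at titration, open-label, V 1 and V-F, but not at S-V or V 0. It marks concomitant medication at every stage.

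**The concern.** Comparing nabilone with the antipsychotic literature treats the two as alternatives. The design instead adds nabilone to whatever stable treatment a participant already takes. For anyone on an antipsychotic, the comparator's own side effects can be part of what is recorded under nabilone. The UKU covers psychotropic side effects in general, and with no rating before dosing, effects that were already present cannot be separated from those that appear afterwards.

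Hypothesis 2 is one of the two hypotheses under the primary objective, and the results are meant to inform a pilot randomised trial and then a multicentre one. A comparative safety statement that does not isolate nabilone would be carried into those designs.

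**Working it through.** **The plan's own figure.** Section 8 contains one calculated figure, and it serves the exploratory objective: 40 × (1 − 0.25) = 30 participants, and a paired t-test at d = 0.53 and two-sided alpha 0.05. The noncentral t with 29 degrees of freedom gives power 0.801, so the figure reproduces. It has no bearing here. Hypothesis 2 has no numerical comparator to reproduce.

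**Inputs for an illustration**

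- f, the share of participants on an antipsychotic: not in the protocol. Assumed range 0.3 to 0.7. The 70% in Section 1.2 is an upper bound and includes other psychotropics.
- pA, the adverse-event rate on an antipsychotic: not in the protocol. Assumed 30%.
- pN, the rate on nabilone alone: assumed 15%, half of pA.
- The two risks act independently: assumed.

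**Case 1: background effects are counted**

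Pooled rate = (1 − f)·pN + f·[1 − (1 − pN)(1 − pA)] = pN + f·pA·(1 − pN).

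- f = 0.3: 0.15 + 0.3 × 0.30 × 0.85 = 0.2265, or 22.7%. This is below 30%, but half of the true 15-point gap has gone.
- f = 0.7: 0.15 + 0.7 × 0.30 × 0.85 = 0.3285, or 32.9%. This is above 30%, although nabilone alone has half the antipsychotic rate.

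Setting the pooled rate equal to pA gives the break-even pN = pA(1 − f)/(1 − f·pA):

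- f = 0.3: 0.21/0.91 = 23.1%.
- f = 0.7: 0.09/0.79 = 11.4%.

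The share at which the reading reverses is f = (pA − pN)/[pA(1 − pN)]:

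- pA = 30%, pN = 15%: 0.15/0.255 = 59%.
- pA = 50%, pN = 40%: 0.10/0.30 = 33%.

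**Direction in Case 1.** The term f·pA·(1 − pN) is never negative, so the pooled rate is never below pN. If the true pooled rate is below pA, then pN is below pA as well. A lower result is therefore conservative. A result that is not lower is ambiguous, because it can come from nabilone or from the background drug.

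**Case 2: only new events are counted**

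Long-standing antipsychotic effects leave the trial's numerator but may remain in the published rates. Participants stable on an antipsychotic are also selected for tolerating it. In addition, a symptom already present cannot be counted as new. Taking only this last effect, and assuming that worsening is not counted, the measured rate is pN(1 − f·pA):

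- f = 0.3: 0.15 × 0.91 = 13.7%.
- f = 0.7: 0.15 × 0.79 = 11.9%.

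Both are below the assumed 15%, so the tilt is now towards nabilone. The protocol does not say which case applies to Hypothesis 2.

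**Size of the antipsychotic-free group.** At f = 0.7 it is 0.3 × 40 = 12 participants. The exact (Clopper-Pearson) upper 95% limit is 1 − 0.025^(1/12) = 26.5% for 0 events in 12, and 38.5% for 1 in 12.

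**The case against.** A reader might infer that the trial can say nothing about relative safety and that any result may mislead. That goes too far. When background effects are counted, the error runs in one direction only, and a lower pooled rate still supports nabilone. The opposite tilt depends on how events are counted and on what the published rates contain, and the protocol gives no figure from which to size it.

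A reader might also take 70% as the antipsychotic share, giving 28 of 40. Section 1.2 does not support this. Its figure is a ceiling, covers all psychotropics and describes adults with IDD in general. The trial also excludes lifetime psychotic and bipolar disorder and current major depression. The assumed event rates have no source in the protocol either. Its own nabilone figures range from about 20% for sedation to 66.0% for drowsiness (Section 9.3).

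Case 1 adds the full antipsychotic rate and is a worst case. The protocol presents the UKU as a measure of study-drug effects, the adverse-event log records start dates, and the PI judges relatedness (Section 12). These safeguards are partial: the judgement is unblinded, all events are logged, and Hypothesis 2 is not limited to related ones.

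Published antipsychotic rates may themselves include other drugs, since polypharmacy is common. This makes the size of the mismatch less certain but does not remove it.

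Finally, tabulation by background drug is often left to an analysis plan. That is fair for the table itself. The comparator and the eligibility rules, however, are fixed in the protocol, and they do not fit together.

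**Conclusion.** The point holds in a limited form. Because stable antipsychotic users may enrol and continue, and no UKU is scheduled before dosing, the percentage set against the antipsychotic literature does not isolate nabilone. With background effects counted, *not lower* cannot be interpreted and *lower* is conservative. With only new events counted, the comparison may favour nabilone.

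The pooled rates of 22.7% to 32.9% against an assumed 30% show that the reading can reverse within a plausible range of antipsychotic use. They rest on assumed rates, an assumed share and independence, and do not estimate the actual bias.

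The description of adverse events on nabilone in this population remains valid; only the comparative conclusion is affected. In a descriptive pre-pilot study with no test or decision rule tied to the comparison, this should be fixed but is not a fatal flaw.

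**What to change.** In Sections 2 and 8:

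1. State that nabilone is added to stable existing treatment.
2. Report each adverse-event percentage with an exact 95% CI, overall and separately for participants with and without a concurrent antipsychotic, using the concomitant-medication record that Table 1 already schedules at every stage.
3. Do not draw the Hypothesis 2 conclusion from the pooled percentage. Keep any comparison with the antipsychotic literature descriptive and base it on participants without an antipsychotic.

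The cost is protocol wording and one extra split of a table. No new data are needed, and eligibility and treatment do not change. The drawback is precision: the antipsychotic-free group may be as small as 12 at the upper end of the assumed range, where a single event moves the upper limit from 26.5% to 38.5%. These participants may also take other psychotropics, so even this group is not strictly nabilone alone. That is why the comparison should stay descriptive.

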### **3. RESEARCH DESIGN/METHODS/ANALYSIS**

#### **3.1. Study Design**

This study is a Phase I pre-pilot open-label trial of nabilone in adults with IDD and SBP. As shown in Figure 1, the trial first includes a screening visit (S-V) for eligibility, then a baseline visit (V 0), followed by a dose titration phase, and then a 4-week open label phase at a stable dose. At the end of the open label phase, participants will undergo a termination visit (V 1), after which nabilone will be tapered off over 8 days. And then, 2 weeks later, participants will undergo a last follow-up visit (V-F) to ensure safety.

At S-V, and before the informed consent process, the participant will be assessed for capacity to provide informed consent. If they cannot pass the competence test using the MacArthur Competence Assessment Tool for Clinical Research (MacCAT-CR), then the written informed consent will be obtained from their substitute decision maker after seeking participants' assent.

At S-V, participants will also be assessed for eligibility based on the inclusion and exclusion criteria, including SBP defined as a score  $\geq 18$  on the Aberrant Behaviour Checklist-Irritability

subscale (ABC-I) and a score  $\geq 4$  on the Clinical Global Impressions-Severity scale (41). The SBP should present with a consistent pattern with the frequency of  $\geq 1$  time per week for  $>3$  months.

If it is deemed necessary, research staff may review participants' medical charts to obtain clinically relevant information and/or additional information to confirm their eligibility. The investigator or research staff may also request information from the participant's physician.

At V 0 the following assessments will be completed:

- Clinical Global Impression – Severity scale (CGI-S) will be rated by the investigator to evaluate the severity of the behavioural problems.
- Measuring baseline vital signs and weight to monitor any AEs of nabilone.
- Assessment of participants' cognitive capacity using the NIH Toolbox® Cognition Battery. Previous evidence suggests that nabilone may cause acute mild decrement in attention and working memory (27). We will use the NIH Toolbox® Cognition Battery, which has been shown as a good candidate outcome measure to examine broad nonverbal cognitive changes for individuals with IDD (valid and reliable for those with a mental age of  $\geq 5$  years; implementable for those with a mental age of  $\geq 3$  years) (42), to assess the baseline attention and working memory.
- Assessment of SBP of participants, including behavioural problems using the ABC-I and Modified Overt Aggression Scale (MOAS), as reported by the caregivers. These scales will be the principal measures for detection of changes in SBP.
- Assessment of anxiety using the parent-rated General Anxiety Subscale of the Anxiety, Depression, and Mood Scale (ADAMS). Nabilone and THC at low doses have been shown to alleviate anxiety, thus this measure is used for exploratory aims to detect a signal of behavioural/mood change with nabilone use.
- Assessment of caregiver's stress and crisis using the Stress Subscale of Depression Anxiety Stress Scales (DASS-21) and Brief Family Distress Scale (BFDS). As SBP cause major caregiver burden, we aim to assess whether the caregiver's stress and distress would improve if nabilone also improves participants' SBP.
- Exploratory assessment of autism symptoms using the Social Communication Questionnaire for Adults with Intellectual Disability (SCQ-AID). Prior evidence suggests that autistic symptoms may be associated with the presentation of SBP (43). We aim to explore whether the baseline autistic symptoms would modulate treatment effects of nabilone.
- Optional assessment of MRI Imaging (dependent on the participant's ability to comply with the following assessments, in the opinion of the carers/parents and investigator).

After V 0, eligible participants will receive open-label nabilone starting with a dosage of 0.25 mg before sleep. During the dose titration phase (which could last up to 15 days), nabilone will be titrated in 0.25 mg increments every two days (with the dosing schedule "twice daily") after consultation with the study team during regular phone calls. This proposed up-titration schedule was decided based on a clinical trial of using Nabilone to treat non-motor symptoms in adults with Parkinson's disease (30). These regular phone calls will be carried out every two days during the whole dose titration phase until the participant reaches a stable dose for the open-label phase. The study team will also check whether the participants show any physical or mental changes which are believed to be attributed to AEs (based on the UKU side effect rating scale), and advise the participant and their caregivers on the next step of titration accordingly. Dose adjustments are

performed until the participant reaches the maximum permitted dose of 1 mg twice daily or experience intolerable AEs believed to be related to nabilone. If intolerable, the participant will use nabilone at the previous lower dose, entering the open label phase. Note that the suggested maximum nabilone daily dose per the product monograph is 6 mg. However, considering the vulnerability of the current target population, we choose to administer 2 mg/day at most in the current proposal following the maximum dose used in clinical trials in people with dementia (27) and Parkinson's disease (30). Moreover, nabilone is a THC analog; THC appears to reduce anxiety at low doses but becomes anxiogenic at high doses. Thus, administering nabilone at lower doses is theoretically consistent with the treatment objective for SBP.

Participants will be then on a stable, optimized nabilone dosage for four weeks, and then the trial ends with an on-site termination visit (V1). During the open-label trial phase, the study team will call the participant and their caregivers once weekly to perform a basic check-up, and to follow up with any questions or concerns from the trial processes. If there are any changes suspected to be associated with AEs, the UKU side effect rating scale will be assessed during the telephone check-up.

At V 1, the following post-treatment assessments will be completed:

- Assessment of adverse events using the UKU side effect rating scale, examined by the researcher or investigator, to systemically investigate the physical AEs of nabilone.
- Re-measuring of vital signs (including blood pressure to check orthostatic hypotension) and weight to monitor the physical AEs of nabilone.
- Re-assessment of participants' cognitive capacity using the NIH Toolbox® Cognition Battery, to monitor any acute cognitive change (AEs) due to nabilone.
- Re-assessment of caregiver rated ABC-I, MOAS, and General Anxiety Subscale of ADAMS. CGI-S and CGI-I will be rated by the investigator to evaluate the severity and improvement of the behavioural problems after nabilone treatment. These re-assessments are implemented to fulfil the exploratory study aim of assessing behavioural changes pre- and post-treatment of nabilone.
- Re-assessment of caregiver's stress and crisis using the Stress Subscale of DASS-21 and BFDS, to investigate changes in their stress and distress after participants takes nabilone.
- Optional re-assessment of MRI Imaging for those who finish the pre-treatment MRI and are willing to receive the second wave of MRI imaging. This is to investigate the change in brain function and structure pre- and post-treatment of nabilone.

Nabilone will be tapered in 0.25 mg daily decrements to prevent acute withdrawal effects. This This proposed down-titration schedule was decided based on a conservative modification from a clinical trial of using Nabilone to treat behavioural and psychological symptoms of dementia (27). Phone calls will be held every other day during the dose-tapering phase, to check whether there are any changes which are believed to be attributed to withdrawal effects. A safety follow-up visit (S-F) will be scheduled after 2 weeks of full discontinuation from the study drug.

The study team will pick up the blister pack from Research Pharmacy, and then distribute to the participant/caregiver. Upon receipt of the nabilone supplies, an inventory will be performed and a receipt log filled out and signed by the research staff who picks up the blister pack. Designated research staff/pharmacy must count and verify that the pickup contains all the items noted in the

shipment inventory. Any damaged or unusable nabilone in a given pick-up will be documented in the clinical trial files. Regarding dispensing the study medication, participants/caregivers will come to CAMH at 3 separate times to pick up nabilone (Table 1), including 1) to pick up the package for the whole dose titration phase and the first 6 days of the stable dose phase at the Pre-treatment Visit (V 0), 2) to pick up the package for the remaining days of the stable phase, and 3) to pick up the package for the dose tapering phase at the Post-treatment Visit (V 1). Nabilone will be prepared for each visit by Research Pharmacy Service. Participants/caregivers will be requested to document the details of using nabilone and other concomitant medications in the drug diary. They will also be asked and expected to return the empty or any leftover nabilone back to the study team, to help with drug accountability.

Regular study intervention reconciliation will be performed to document nabilone assigned, consumed, and remaining. This reconciliation will be logged on a drug accountability log, and signed and dated by delegated research and/or pharmacy staff.

At the completion of the clinical trial, there will be a final reconciliation of the nabilone dispensed, consumed and remaining, based on the drug diary, the remaining drugs which are returned. This reconciliation will be logged on an accountability form, and signed and dated by delegated research and/or pharmacy staff. Any discrepancies noted will be investigated, resolved, and documented prior to return or destruction of unused study intervention. Intervention destroyed on site will be documented in the clinical trial's files.

All participants entering the dose titration phase will be included in the description of the safety profile and tolerability of nabilone (the Primary Objective). Participants completing the dose titration stage will be included in the final statistical analysis for the Exploratory Objective (i.e., explore changes in SBP in participants pre-and post-treatment), regardless of whether they complete the full protocol. This approach is consistent with the intention-to-treat principle.

**Figure 1.** A schematic diagram of the study procedures, including all study visits and timelines. Abbreviation: S-V: a screening visit; V 0: a baseline visit; V 1: a visit at the end of open label phase; V-F: a follow-up visit to ensure safety; d: days; wk: weeks; FU: follow-up; max: maximum.

[figure not shown]

**Table 1.** Schedule of study visit procedures and assessments

|                                                   | Screening
(S-V) | Pre-
Treatment
(V 0) | Titration | Open-
label | Post-
Treatment
(V 1) | Safety
Follow-
up (V-F) | Visit
option        |
|---------------------------------------------------|--------------------|----------------------------|-----------|----------------|-----------------------------|-------------------------------|------------------------|
| Informed
Consent                       | •                  |                            |           |                |                             |                               |                        |
| Demographics                               |                    |                            |           |                |                             |                               |                        |
| Dx of IDD and
comorbidities
(Moss-PAS (ID)) | •                  |                            |           |                |                             |                               | Either or a |
| Age                                               | •                  |                            |           |                |                             |                               | Either or              |
| Sex/Gender                                        | •                  |                            |           |                |                             |                               | Either or              |
| Height                                            | •                  |                            |           |                |                             |                               | In person              |
| Weight                                            | •                  | •                          |           |                | •                           | •                             | In person              |
| Competence
(MacCAT-CR)                         | •                  |                            |           |                |                             |                               | Either or              |
| Concomitant
medication                         | •                  | •                          | •         | •              | •                           | •                             | Either or              |
| Adaptive
function
(ABAS-3)                  | •                  |                            |           |                |                             |                               | Either or              |
| Compliance                                        |                    |                            |           |                | •                           |                               | Either or              |
| Safety Outcome                             |                    |                            |           |                |                             |                               |                        |
| PE, Vital signs                                   | •                  | •                          |           |                | •                           | •                             | In-person              |
| Pregnancy                                         | •                  |                            |           |                |                             |                               | In-person              |
| AEs (UKU)                                         |                    |                            | •         | •              | •                           | •                             | Either or              |
| NIH-Toolbox                                       |                    | •                          |           |                | •                           | •                             | In-person              |
| Clinical Effect Outcome                    |                    |                            |           |                |                             |                               |                        |
| Primary                             |                    |                            |           |                |                             |                               |                        |
| ABC-I                                             | •                  | •                          |           |                | •                           |                               | Either or              |
| Secondary                           |                    |                            |           |                |                             |                               |                        |
| MOAS                                              |                    | •                          |           |                | •                           |                               | Either or              |
| Anxiety-
ADAMS                                 |                    | •                          |           |                | •                           |                               | Either or              |
| Stress-DASS-21                                    |                    | •                          |           |                | •                           |                               | Either or              |
| BFDS                                              |                    | •                          |           |                | •                           |                               | Either or              |
| CGI-S                                             | •                  |                            |           |                | •                           |                               | Either or              |
| CGI-I                                             |                    | •                          |           |                | •                           |                               | Either or              |
| Exploratory                         |                    |                            |           |                |                             |                               |                        |
| SCQ-AIQ                                           |                    | •                          |           |                |                             |                               | Either or              |
| MRI (optional)                                    |                    | •                          |           |                | •                           |                               | In-person              |

| Nabilone Dispense        |  |   |  |   |   |   |           |
|--------------------------|--|---|--|---|---|---|-----------|
| Pick-up                  |  | • |  | • | • |   | In-person |
| Return (if applicable)   |  |   |  | • | • | • | In-person |
| Acceptability Evaluation |  |   |  |   |   | • | Either or |

Abbreviation: Dx = diagnosis; MacCAT-CR = MacArthur Competence Assessment Tool for Clinical Research; Moss-PAS (ID) = Moss Psychiatric Assessment Schedules; ABAS-3 = Adaptive Behavior Assessment System, Third Edition; PE = physical examination; AE = adverse event and severe adverse event; NIH-Toolbox = NIH Toolbox® Cognition Battery; ABC-I = Aberrant Behavior Checklist-Irritability Subscale; MOAS = Modified Overt Aggression Scale; CGI-I = Clinical Global Impressions (CGI) scale-Improvement; CGI-S = Clinical Global Impressions (CGI) scale-Severity; Anxiety-ADAMS = General Anxiety Subscale of Anxiety, Depression, and Mood Scale; Stress-DASS-21 = Stress Subscale of the short-form version of Depression Anxiety Stress Scales; BFDS = Brief Family Distress Scale; SCQ-AIQ = Social Communication Questionnaire for Adults with Intellectual Disability.

a: Either in-person or virtual visit

